#### Primary outcome

KOA is characterized by knee pain as its predominant symptom. Visual Analog Scale (VAS) scores, ranging from 0 to 100 mm, are utilized to objectively quantify pain levels. The primary outcome of this study is the difference in VAS scores between day 14 and baseline measurements. Participants are instructed to indicate the severity of their knee pain by marking a point on a continuous horizontal line segment, with 0 mm representing minimal pain and 100 mm indicating the most severe pain [28].

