#### Secondary outcomes

**VAS:** We assess patients’ knee pain using the VAS at baseline, on day 7 and during the follow-up period as secondary outcome indicators.**WOMAC:** The Western Ontario and McMaster Universities Arthritis Index (WOMAC) is widely used to assess the clinical manifestations of knee disorders. We assess the WOMAC scores at baseline, on day 7, day 14, and during the follow-up period. The WOMAC index consists of three sections including evaluation of pain (5 questions), stiffness (2 questions), and physical function (17 questions). A five-level scoring system is applied for each question: asymptomatic (0 point), mild (1 point), moderate (2 points), severe (3 points), and very severe (4 points). Participants complete the index according to their actual conditions. Higher scores indicate more severe symptoms [29]. The temporal evolution of WOMAC scores is analyzed within each group. The scores on each assessment day are also compared between the two groups.**ROM:** Range of Motion (ROM) is evaluated to visually record the motion angle of knee joint. Active ROM, including flexion and extension, is measured at baseline, on day 7 and day 14. For active flexion ROM, the participant are positioned prone with knees at the bed’s edge and lower legs extended naturally. The participant then flexes the knees maximally. Thus, the flexion angle is recorded. For active extension ROM, the participant lies supine with lower limbs extended and ankles slightly elevated by a cushion. The participant then extends the knees maximally. Thus, the extension angle is recorded [30, 31]. Measurements are repeated three times and averaged. Generally, abnormal restriction of active ROM is associated with adhesion of joint cavity, contracture of tendons and muscle weakness. The improvement in active ROM indicates knee healing. Thus, active ROM is evaluated to compare the efficacy of the interventions. (Fig. 4)**Three-dimensional Gait Analysis:** An Opti-Knee 3D motion analysis system equipped with Guangdong Provincial Hospital of Chinese Medicine is used to detect the motion data of the knee joint. The parameters of six degrees of freedom (6 DOFs) are collected and analyzed. The indicator is detected on day 0, day 7 and day 14. The knee joint exhibits complex motion, primarily resulting from the relative movement of the tibia and femur. Based on the principles of the anatomical coordinate system, a three-dimensional femur-tibia coordinate system is established. Thus, it allows the decomposition of the relative motion between the tibia and the femur into 6 DOFs. The DOFs rotating around the coordinate axes includes: internal/external rotation angle, internal/external flip angle, flexion/extension angle. The DOFs translated along the coordinate axes includes: anterior/posterior displacement, superior/inferior displacement, and internal/external displacement [32, 33]. During practice, the participant is asked to undergo approximately 2–3 min of acclimatization. After the bony marks on the body surface are ready for positioning, the participant walks continuously on the exercise board in a natural habitual way at a constant speed of 3.0 km/h. Subsequently, the system collects gait data of 6 DOFs at a frequency of 60 frames/s and an acquisition time of 15 s. The temporal evolution of gait parameters is depicted through curves, and the data are then exported in the form of single-cycle gait data (Fig. 5). In our results, we concentrate on three primary aspects: a comparison of 6 DOFs of the affected knee and those of the healthy side; the evolution of 6 DOFs over the treatment course within the same group; and a comparison of 6 DOFs discrepancies between the two groups. By modeling the participants’ habitual flat walking patterns, we investigate whether the kinematic deficiencies of the affected knee demonstrate an improvement post-treatment, or if the kinematic characteristics of both knees exhibit a tendency to converge.**Shear Wave Elastic Imaging Technology Analysis:** The mean elastic modulus serves as an indicator of muscle tone, which is associated with knee stiffness. We evaluate the Young’s modulus of major muscle groups of knee joint at baseline, on day 7 and day 14. A Supersonic Aixplorer Color Doppler Ultrasound Diagnostic Unit equipped with Guangdong Provincial Hospital of Chinese Medicine is used. Lying flat on the bed, the participant is instructed to relax all body muscles and to straighten both legs naturally. First, 2D ultrasound is used to identify the major muscles. The device is then switched to the SWE mode, with an L15-4 line array probe and a frequency of 4–12 MHz. With the ultrasound set to muscle examination mode, we sequentially measure the vastus intermedius, rectus femoris, vastus lateralis, and tibialis anterior muscles. The probe is lightly placed at the midpoint of the examined muscle belly, and it is parallel to the direction of the muscle fibers. With no pressure applied, skeletal muscles can be regarded as having three layers of depth: the upper layer, the middle layer, and the lower layer. In the ultrasound display, the middle layer is selected to place the sampling box for quantitative analyses. After 5 s, the image is frozen as the shear wave pattern in the box is stable and uniform. The Q-BOX function is launched, with the measurement area set as a 5-mm circle. The system then automatically calculate the mean value of Young’s modulus for the muscle tissues in the Q-BOX (Mean). Each frozen image with the calculation is repeated 3 times, and the mean values of 2 qualified sampling boxes are taken for statistical analyses (Fig. 5). Prior studies have suggested that the higher the value of the elastic modulus of the muscles around the knee, the higher the muscle tone and the tighter the epimysia, which results in restriction to the contraction of muscle fibers and function of the knee joint [34–36]. However, other studies have either failed to find significant results [37] or have reached contrary conclusions [38]. In response to these mixed findings, we investigate the elastic modulus of the major muscles along the force line of the lower extremity, aiming to provide credible evidence.

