### Statistical analysis

All the statistical tests are conducted using a bilateral test, with *P* < 0.05 indicating a statistically significant difference. The Mean ± standard deviation is used for normally distributed measurement data. Non-normal data are presented as the median and interquartile range. Differences in data on outcome measures from baseline to each evaluation time point are analyzed using independent sample t tests or Mann–Whitney U tests, as appropriate, between groups; paired t tests or Wilcoxon tests are used to compare differences in the data for each outcome index at each evaluation time point within the group. In addition, the VAS and WOMAC evaluations are repeated 5 times in this study. Therefore, repeated measures analysis of variance are used for auxiliary analysis. Baseline data (including age, sex, BMI, etc.) are controlled for as confounding factors. Multiple imputation methods are adopted for the analyses of missing data. A generalized linear mixed model is further used for analyses of non-normal and partially missing data, as the interaction effects are also analyzed. The intention-to-treat analyses are performed for the outcomes. SPSS 25 software (IBM SPSS Statistics, New York, USA) is used for the data analyses. Data analyses are conducted by a data analyst who is unaware of allocation and treatment.

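### Free improvement: make a baseline-adjusted ANCOVA the primary analysis of VAS, because the planned t test or Mann–Whitney on change cannot carry the promised baseline control

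*Protocol article*

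**What the plan says.** The Primary outcome section defines the endpoint as a change: "The primary outcome of this study is the difference in VAS scores between day 14 and baseline measurements". The Sample size calculation section works with a difference of 6.5 mm between the groups' mean changes, an SD of 3.85 mm taken from a reference trial, and a non-inferiority margin of 10 mm.

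The Statistical analysis section then makes four statements that bear on the between-group comparison:

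- "Differences in data on outcome measures from baseline to each evaluation time point are analyzed using independent sample t tests", or by Mann–Whitney, the choice depending on which is suitable.
- For VAS and WOMAC, measured five times, "repeated measures analysis of variance are used for auxiliary analysis".
- "Baseline data (including age, sex, BMI, etc.) are controlled for as confounding factors". No model is attached to this sentence, and baseline VAS is not in the list.
- "A generalized linear mixed model is further used for analyses of non-normal and partially missing data", with interaction effects also examined.

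No analysis is expressly labelled primary. That the two-sample test holds this place follows from the order and from the words used for the other models.

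**The concern.** A two-sample t test and a Mann–Whitney test have no place for a covariate. The promise to control for baseline data can therefore apply only to the auxiliary or further models, not to the comparison that leads the analysis. The variable most worth adjusting for, baseline VAS, is not named at all.

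A change score subtracts baseline but generally leaves the result correlated with it. Part of the noise that baseline could explain stays in the estimate, and a chance difference in baseline pain between two arms of 30 carries over into the treatment effect.

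The switch to Mann–Whitney adds a second problem. The design is stated in terms of mean changes and a 10 mm margin, and a rank test does not deliver a mean difference with an interval to compare with that margin. Whether the trial produces such an estimate from its leading test would depend on how the data turn out to be distributed.

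**Working it through.** **Inputs from the article.** 60 participants, 1:1, 10% dropout: 60 × 0.9 / 2 = 27 evaluable per arm. SD of change 3.85 mm. Expected difference 6.5 mm.

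**Assumptions (not in the article).** Correlation ρ between baseline and day-14 VAS of 0.3 to 0.7, and equal SDs at the two visits unless stated otherwise. A baseline SD of 15 mm is used as a second scenario.

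**The plan's own figure.** The article gives no figure for the efficiency of its test. Its total of 60 does not follow from 6.5 mm, SD 3.85 mm and 80% power (an exact t calculation needs 7 per arm before dropout), but that is a separate matter. The comparison below depends on ρ and the SD ratio, not on the sample size.

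**Step 1: variance.** Write s for the baseline SD.

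- Change score: 2(1 − ρ)s². ANCOVA residual: (1 − ρ²)s². Ratio: (1 + ρ)/2.

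| ρ | Variance ratio | SE ratio | 27 per arm is worth, under the change score |
|---|---|---|---|
| 0.3 | 0.65 | 0.81 | 27/0.65 = 41.5 |
| 0.5 | 0.75 | 0.87 | 27/0.75 = 36.0 |
| 0.7 | 0.85 | 0.92 | 27/0.85 = 31.8 |

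If the day-14 SD is k times the baseline SD, the change-score variance exceeds the ANCOVA variance by (1 − ρk)²s², which is never negative. The price is one degree of freedom. A small-sample factor of 1 + 1/50 moves the ratios to 0.663, 0.765 and 0.867.

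**Step 2: simulation.** 5,000 trials per ρ, 27 per arm, with the SD of change set at 8.37 mm. This is the value at which 27 per arm gives 80% power for 6.5 mm; it is an assumption. Mean SEs, change score against ANCOVA, were 2.264 against 1.844 (ρ = 0.3), 2.258 against 1.980 (0.5) and 2.265 against 2.109 (0.7). Power went from about 0.80 to 0.93, 0.89 and 0.84.

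**Step 3: the article's SD.** At 3.85 mm and 27 per arm, power for 6.5 mm is already 1.00 to three decimals, so the gain shows in the interval. The approximate 95% half-width is 1.96 × 3.85 × √(2/27) = 2.05 mm for the change score. Multiplied by the SE ratios (0.806, 0.866, 0.922), it is 1.66, 1.78 and 1.89 mm for ANCOVA.

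**Step 4: chance imbalance.** A baseline difference d shifts the change-score estimate by (1 − ρ)d in size. At ρ = 0.5:

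- SD of change 3.85 mm implies s = 3.85/√(2 × 0.5) = 3.85 mm. The 95% range of d is ±1.96 × 3.85 × √(2/27) = ±2.1 mm, and of the shift ±1.0 mm. Over ρ from 0.3 to 0.7 the shift limit runs from about 1.2 down to 0.8 mm.
- s = 15 mm: d within ±1.96 × 15 × √(2/27) = ±8.0 mm, and the shift within ±4.0 mm. Over the same ρ the limit is 0.7 × 8.0 = 5.6 down to 0.3 × 8.0 = 2.4 mm.

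Steps 1 and 4 describe one gain, not two. The variance of the shift is (1 − ρ)²s² per unit, which is exactly the excess 2(1 − ρ)s² − (1 − ρ²)s².

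**The case against.** The strongest reply is that nothing here is an error. The endpoint is defined as a change and the sample size rests on the difference in mean changes, so a two-sample test on change matches both. Under randomisation it is unbiased, and its standard error already includes chance baseline imbalance. All of that stands.

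A second reply is that adjustment is planned: the covariate list is left open, VAS is among the pre-intervention assessments, a mixed model is named, and a condensed article may leave model details to a fuller document. This also stands in part. A reader might infer that the plan contains no adjustment, and that would be wrong. What remains is that the article does fix the leading test, and that test cannot carry the stated control.

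Other, stronger readings are tempting but not supported:

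- That the repeated measures ANOVA undermines the intention-to-treat aim by needing complete data. The article plans multiple imputation and assigns the mixed model to partially missing data.
- That counting baseline as one of five levels shrinks the treatment effect. This concerns only the group main effect of an auxiliary analysis. The article does not make that effect its estimate, and it mentions interaction effects with the mixed model.
- That WOMAC is handled inconsistently. "The scores on each assessment day are also compared between the two groups" is an addition to the change comparison, not a conflict with it.
- That imbalance of 8 mm is to be expected. With an assumed baseline SD of 15 mm, ±8 mm is the range that contains 95% of trials, so only about 1 in 20 would go beyond it.

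**Conclusion.** The point holds as a free improvement, not as a fault that invalidates the test. The leading comparison is valid but leaves baseline information unused, does not fit the covariate sentence beside it, and in its Mann–Whitney form gives no mean difference to set against 10 mm.

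The direction of the gain is certain apart from one degree of freedom. Its size rests on ρ, which the article does not give: an SE about 19%, 13% or 8% smaller at 0.3, 0.5 or 0.7 with equal SDs. The protection against chance imbalance, at ρ = 0.5, is worth about ±1 mm if the SD of 3.85 mm holds and ±4 mm if the baseline SD is 15 mm. In the first case the benefit is interval width only; a material gain in power needs a larger SD than the article assumes.

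**What to change.** - **Primary analysis.** State one: ANCOVA of day-14 VAS on treatment and baseline VAS, with age, sex and BMI added if they are prespecified. Report the adjusted mean difference and 95% CI whatever the distribution looks like, and hold that interval against the 10 mm margin. The endpoint need not be redefined, because regressing change on treatment and baseline VAS gives the same treatment estimate.
- **Sensitivity analyses.** Keep the t test and Mann–Whitney here.
- **Covariate sentence.** Say which models it applies to, and list baseline VAS.
- **Repeated measures.** Replace the ANOVA by a linear mixed model of the post-baseline visits, with the baseline value as covariate and treatment-by-visit terms: four visits for VAS and WOMAC (days 7, 14, 28 and 42), two for ROM, gait and elastography (days 7 and 14).

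The cost is a change of wording in the analysis plan, made before the data are unblinded. No new data are needed, and the planned software can fit these models.

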### Ethics

The research results of this project may be published in medical journals, but we will keep the patient’s information confidential by legal requirements. Unless required by relevant laws, the patient’s personal information will not be disclosed. When necessary, government management departments, hospital ethics committees, and their relevant personnel can access patient information according to regulations. Researchers or researchers who are authorized personnel are responsible for explaining the benefits and risks of participating in the trial to each patient, their legal representative, or a notary witness and should obtain written informed consent before the patient enters the trial. The original informed consent form signed and dated by all participants or their legal representatives, as well as the person presiding over the informed consent process, will be kept by the researchers.

### Dissemination and data sharing

The study will be reported according to the Consolidated Standards of Reporting Trials (CONSORT) statements. The results of their data will be disseminated to participants through interviews held with nurses. The final manuscript will be completed by the first two authors and the authorship of the final manuscript will depend on the actual contribution. The study results will be distributed using a broad dissemination strategy, including oral presentations at international meetings and publications in peer-reviewed international journals.

## Discussion

This study evaluates the effectiveness of FSN for the treatment of senile knee osteoarthritis compared to that of NSAIDs in terms of pain, self-reported function, gait, and muscle flexibility and assesses the differences in adverse events between the two interventions.

The main therapeutic objectives of KOA are to reduce pain, improve knee function, control arthritic symptoms, and enhance patients’ quality of life. In addition to weight loss and functional knee exercises, NSAIDs are consistently recommended by all guidelines as the first-line therapeutic agent to relieve pain [44, 45]. However, long-term application of NSAIDs carries the risks of gastrointestinal bleeding, cardiovascular adverse events, and nephrotoxicity. In addition, symptoms tend to recur once the drug is discontinued. For the elderly population, the risk of adverse reactions caused by NSAIDs is even greater. For example, the incidence of upper gastrointestinal bleeding is greater than that of other age groups, and the extent of the lesions is more severe [42, 43]. In the early or middle stage of KOA, to prevent the disease from progressing to an advanced stage that is difficult to reverse, clinical guidelines in various countries recommend treatments such as appropriate physiotherapy and muscle functional training, which aim to correct the pathological biomechanical imbalance of the affected knee joint [46, 47]. Therefore, in addition to medication, aggressive early intervention with complementary therapies for KOA may be of important.

As a newly emerging acupuncture method, FSN can also be used to treat KOA. Previous studies have suggested that FSN significantly relieves pain as well as joint stiffness and swelling and improves quality of life in patients with KOA [22, 23]. However, the biochemical mechanism by which FSN exerts its therapeutic effect remains unclear. The possible mechanism of action of FSN is that it improves blood circulation and muscle function. The significance of the Swaying Movement may be primarily related to mechanical, electrophysiological and biochemical effects in loose connective tissue [48, 49]. The Reperfusion Approach induces sudden compression and contraction of blood vessels in the involved muscles, followed by immediate vasodilation [50]. With blood circulation and tissue perfusion greatly accelerated, the vicious circle of Energy Crisis is interrupted [51]. These combined effects are believed to adjust the force lines of the lower limb. As the abnormal pressure on the cartilage decreases, it helps to maintain the stability of the knee joint, eventually allowing the forces on the joint to tend toward a normal balance.

The advantages of our study design are as follows: First, we rigorously designed and will conduct this trial to assess the effectiveness of FSN in treating KOA to provide evidence for decision-making and promotion of relevant complementary and alternative therapies; second, with the use of advanced instruments or equipment, we are the first to measure exploratory objective indicators to determine the mechanism of action of FSN in treating senile KOA from a biomechanical point of view, which can similarly provide clues for further research on FSN therapy and support its clinical application.

An evident limitation of this study is that, due to the inherent natures of acupuncture and medication, it is challenging to blind both the operators and the participants. This lack of blinding may increase the risk of bias. Consequently, the results of this study will be carefully evaluated and interpreted with a critical perspective. To minimize other potential sources of bias, the intervention operators, outcome assessors, data collectors, and data analysts act as independent investigators. Researchers, other than the intervention operators, shall not be aware of the group assignments of the participants. Additionally, instructions are provided throughout the trial to ensure that the participants undergo treatments and evaluations as planned, thereby avoiding potential implications of unplanned treatments on the outcome assessment. However, it is worth noting that the therapeutic effects of acupuncture are considered to involve both physical and psychological aspects [52]. Generally, the practice of acupuncture requires adjustment of patients’ mental state [53]. As a new method of acupuncture, the therapeutic effects of FSN are potentially diverse, encompassing direct physical effects and potential psychological effects. Thus, a placebo effect may actually be involved. The results of this study have the potential to inform further research. The combined curative effects of FSN could be analyzed from different perspectives, focusing separately on various mechanisms of action.

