Currently, acupuncture has been increasingly used in the practice of KOA treatment, effectively relieving the symptoms of pain and joint stiffness [15, 16]. A large-sample, multicentre study found that electroacupuncture treatment for KOA achieved a response rate of 60.3% at Week 1, and demonstrated satisfactory long-term effects at Week 26 [17]. Fu’s subcutaneous needling (FSN) is an emerging acupuncture modality, characterized as safe, eco-friendly and efficient. It has been used in clinical practice for more than 20 years. The practitioner uses a specially designed needle to perform horizontal reciprocal swaying within loose connective tissues under the skin, in conjunction with the Reperfusion Approach. FSN therapy is distinguished by its rapid onset of effect [18]. A meta-analysis showed that FSN significantly treated KOA and had a faster onset of effect than did manual acupuncture, drugs, and herbal medicine [19]. The only target objects for FSN are muscles under pathological tension. It has been demonstrated that the reciprocal Swaying Movement of the FSN in the loose connective tissue and the Reperfusion Approach of muscle contraction-diastole elevate the perfusion of vascular blood flow through the interosseous space [20]. This restores healthy muscle elasticity [21] and further restores joint stability of the knee, thereby having a therapeutic effect on KOA. We hypothesized that this is the reason why FSN is effective.

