Our preliminary study revealed that the modulus of elasticity of the lateral femoral muscle was significantly higher on the affected side than on the healthy side in patients with KOA (*p* < 0.01). It was also found that FSN significantly improved symptoms and signs while reducing the modulus of elasticity of the lower limb skeletal muscles (vastus lateralis, tibialis anterior, and gastrocnemius) of KOA patients (*p* < 0.05), and a related paper is being prepared for publication. Previously, two studies have suggested that FSN therapy applied for the treatment of KOA effectively relieved pain [22, 23]. However, both studies only applied pain-related measures or function-related measures as indicators of efficacy. Few studies have focused on a biomechanical point of view. There are also few published clinical studies that have used objective measures other than scales, such as ultrasonography or imaging. Therefore, the objective of this randomized clinical trial is to investigate the clinical effects and biomechanical mechanisms of FSN for the treatment of elderly patients with knee osteoarthritis. We hypothesized that an intervention programme using FSN for 2 weeks, 3 times per week, would produce better improvements in pain as well as physical function of the knee compared to a positive control group taking celecoxib. Furthermore, this clinical trial also aims to evaluate the ability of FSN to improve gait and lower limb muscle flexibility, which may further help explore the mechanism of FSN therapy.

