### FSN therapy

Operation of the FSN follows the KOA’s Fu’s Subcutaneous Needling Treatment Code of Practice [27]. Participants first assume the supine position. After routine disinfection, a disposable Fu’s subcutaneous needle (Nanjing Paifu Medical Technology Co., Ltd., Jiangsu, China, Fig. 2) is inserted parallel into the subcutaneous loose connective tissue around the pathological tight muscles (gastrocnemius muscle, tibialis anterior muscle, and quadriceps femoris muscle). The protruding part of the hose holder is fixed to the card slot after the needle is completely inserted. Confirming that the participants have no pain, the index and ring fingers alternate back and forth in a smooth, soft, fan-like swaying movement. The fan angle is approximately 60°, and a total of 45 round trips are performed in 30 s. Swaying Movement is accompanied by Reperfusion Approach: 20 sways along with 10 s of Reperfusion Approach are performed as a set of procedures. For each target pathological tight muscle, 2–3 sets of the above procedures are required. The Reperfusion Approach for different pathological tight muscles are as follows: (1) for the gastrocnemius muscle, the participant is placed in the prone position, with the foot extended out of the bed. A towel is placed on the soles of the feet, and the participant is instructed to resist resistance by plantar flexion of the ankle joint; (2) for the tibialis anterior muscle,the participant is placed in the supine position, and the ankle is dorsiflexed to resist counterdirectional forces from the instructor, (3) for the quadriceps muscle,the participant is placed in the supine position. With a foam shaft or other support made of soft material placed in the popliteal fossa, the knee joint is then forcefully extended against resistance from the instructor. The FSN group is treated 3 times a week for 2 weeks. Prior each FSN treatment day, participants are contacted by telephone in advance to schedule specific sessions and are reminded to attend. (Fig. 3).

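### The mechanism wording goes further than the stated analyses: muscle and gait changes are never related to pain change or to baseline stiffness, so a difference could be a consequence of pain relief

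*Protocol article*

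**What the plan says.** **The aim.** The Introduction gives the objective as "to investigate the clinical effects and biomechanical mechanisms of FSN for the treatment of elderly patients with knee osteoarthritis". Among the design advantages, the Discussion lists that "we are the first to measure exploratory objective indicators to determine the mechanism of action of FSN in treating senile KOA". Elsewhere the aim is more modest. The Introduction says that gait and muscle flexibility are evaluated, "which may further help explore the mechanism of FSN therapy", and the Abstract and the Conclusion also speak of exploring.

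**The postulated chain.** According to the Introduction, "The only target objects for FSN are muscles under pathological tension". FSN is said to restore their elasticity, this restores knee stability, and the therapeutic effect follows.

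**The analyses.** Statistical analysis states: "Differences in data on outcome measures from baseline to each evaluation time point are analyzed using independent sample t tests or Mann–Whitney U tests". It adds paired tests within each group. Secondary outcomes lists three gait comparisons: affected against healthy knee, change over treatment within a group, and difference between groups. Repeated-measures analysis of variance is described for VAS and WOMAC. A generalized linear mixed model is mentioned together with interaction effects that are not defined.

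**The timing.** Modulus and gait are measured on days 0, 7 and 14. VAS is measured on days 0, 7, 14, 28 and 42.

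**The concern.** The mechanism claim is about order and dependence: muscle tension falls first, and pain falls because of it. Differences between groups, over time or between sides do not test order or dependence. If pain falls first, for whatever reason, and the patient then relaxes the muscles and walks better, the same differences appear.

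The plan gives grounds to take this rival path seriously. The sample size section assumes that VAS change differs between the arms by 6.5 mm at two weeks, so unequal pain relief is expected. Participants are not blinded, and the Discussion accepts that psychological and placebo effects may be involved. Secondary outcomes also reports that earlier studies disagree on how modulus relates to muscle tone and knee function, so the link cannot be taken as known.

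At stake is what the trial may conclude on a stated objective. It could report that modulus or gait differed between arms. It could not, from the stated analyses, say that this is how FSN works.

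**Working it through.** **Step 1. Each link of the chain against the stated analyses.**

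| What the mechanism claim needs | What the article states |
|---|---|
| Modulus or gait changes more with FSN | Between-group test of change: yes |
| Modulus or gait changes over time | Paired tests within group: yes |
| Affected knee moves toward the healthy one | Gait comparison by side: yes |
| The change is greater where the muscle was stiff | Not stated; baseline enters only through subtraction in the change score |
| Muscle or gait change is related to pain change | Not stated |
| Muscle change comes before pain change | Not stated, although the visits would allow it |

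The first three rows are the same under both orders of events. Only the last three bear on mechanism.

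**Step 2. Target and measurement.** Eligibility does not require a tight muscle. Elastography covers a fixed list (vastus intermedius, rectus femoris, vastus lateralis, tibialis anterior) whatever the baseline tension. The gastrocnemius is needled (FSN therapy), and its modulus is among those reported to have fallen in the preliminary work (Introduction), yet it is not on the imaging list.

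**Step 3. What a linking analysis could detect.** The plan gives no figure for the mechanism aim; its N of 60 is set on VAS. With the plan's 10% dropout, 60 × 0.90 = 54 completers, or 27 per arm.

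- Smallest correlation detectable with 80% power, two-sided 0.05, by Fisher z: tanh[(1.960 + 0.842)/√(n − 3)].
  - n = 54: tanh(2.802/√51) = 0.37.
  - n = 27 (FSN arm alone): tanh(2.802/√24) = 0.52.
- Bare significance threshold at n = 54: tanh(1.960/√51) = 0.27. A true correlation of that size is found only about half the time.
- Number needed for 80% power, [2.802/atanh(r)]² + 3: 194 for r = 0.2, 85 for r = 0.3, 47 for r = 0.4, 30 for r = 0.5.

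**Step 4. Both links together.** The power to find both an arm effect on the marker and a marker–pain association is approximated as the product of the two powers, with 27 per arm. The effect sizes are assumptions; the documents give none.

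| Arm effect (SD) | Partial r | Power |
|---|---|---|
| 0.3 | 0.2 | 0.196 × 0.299 = 6% |
| 0.5 | 0.3 | 0.451 × 0.590 = 27% |
| 0.8 | 0.3 | 0.836 × 0.590 = 49% |
| 0.8 | 0.5 | 0.836 × 0.973 = 81% |

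**Step 5. Baseline adjustment.** With equal variances at both visits and baseline–follow-up correlation r, the variance of the adjusted comparison relative to the change-score comparison is (1 − r²)/(2 − 2r) = (1 + r)/2. This is below 1 for any r below 1, so the covariate costs nothing and gains precision.

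**The case against.** **The aim is exploratory.** The Discussion sentence itself calls the indicators exploratory and goes on to speak of clues for further research. The Abstract, part of the Introduction and the Conclusion also speak of exploring, and the Discussion leaves the separation of mechanisms to later work. For such an aim, describing biomechanical change is legitimate. This stands, and it limits the point to a mismatch between the strongest wording and the stated analyses. It does not remove the mismatch, because mechanisms are also part of the stated objective.

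**Further models may be in an analysis plan.** That plan is not shown, and the undefined interaction effects might include one. The absence of a lagged model from an article is therefore not an error in itself. What remains is that the claim, as printed, goes further than the analyses printed with it.

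**A reader might infer more than the documents support.**

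- *That the markers are compared only between arms.* They are not: within-arm and side-to-side comparisons are also planned.
- *That the mechanism question cannot be addressed at all.* The visit schedule permits an exploratory analysis of order.
- *That the preliminary study found raised modulus in the lateral femoral muscle only, so the other muscles had nothing to correct.* The Introduction reports that muscle, does not say the others were normal, and reports falls in three muscles after FSN. If only a fraction p of the measured muscles could respond, the sample needed would grow by 1/p² (1.6 times at p = 0.8, 4 times at p = 0.5), but no value of p has a source in the documents.

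**The linking analysis is weak.** This is correct. Power is low, confounding of modulus and pain remains, and the rapid onset claimed for FSN means that both changes may be complete before day 7. It should not decide whether mechanism wording is allowed.

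**Conclusion.** The concern holds in limited form. The stated analyses can show that modulus or gait differs between arms, over time or between sides. They cannot separate a cause of pain relief from a consequence of it, and they do not ask whether any effect occurs where muscles were stiff at baseline. Wording that promises to *determine* the mechanism is not supported; wording that says *explore* is.

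The effect is on interpretation of a stated objective. The primary VAS comparison does not depend on it. An added linking analysis could detect, with 80% power, only a correlation near 0.37 overall or 0.52 within the FSN arm. This assumes 54 completers, roughly normal changes and the simple Fisher approximation; covariates would raise these values slightly.

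**What to change.** All three changes use measurements already scheduled.

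1. **Modulus between arms.** Include baseline modulus as a covariate, and add the baseline-by-arm interaction as exploratory, so that the effect is also described where the muscle was stiff.
2. **One prespecified exploratory linking analysis.** Relate modulus change to VAS change, adjusted for arm and baseline VAS, in both time orders: modulus change from day 0 to 7 against VAS change from day 7 to 14, and the reverse. Name the muscle in advance. State that about 54 completers give 80% power only for correlations near 0.37, that effects complete before day 7 may be missed, and that confounding cannot be excluded.
3. **Wording.** Whatever that analysis shows, report modulus and gait results as biomechanical effects that may help explore the mechanism. Align the objective in the Introduction and the design-advantage sentence in the Discussion with the exploratory wording of the Abstract and the Conclusion.

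The cost is two imprecise exploratory models and a more modest claim. No new visit, measurement or participant is needed.
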